#### *Sample size*

We will randomly select eight long-term care homes that agree to join this study. As no similar cluster-randomized trial has been reported in the literature, we can only estimate the intracluster coefficient with a range between 0 and 0.1 [22]. The intensity of pain can vary according to the different natures and sources of the pain. As this study is not limited to participants suffering from a particular type of pain, we anticipate that variations in the nature of participants’ pain will be considerable. Due to its heterogeneous nature, we assumed an intracluster correlation of 0.02. The pilot study was able to detect a mean difference of 13.41 points on the MSQ score (95% confidence interval 8.923 to 17.897) and -0.3 points on the C-PAINAD (95% confidence interval -4.459 to 0.169) between the pre- and post-tests [18]. After averaging the effect sizes calculated based on these two mean differences, this was equivalent to an effect size of 0.65. In order to secure an appropriate effect size, a more conservative approach of using an effect size of 0.4 was used to calculate the sample size. With a significance level (α) of 0.05 and power (1-β) 0.8 for a two-sided test, the sample size calculation gives about 38 participants for each group in order to evaluate a mean difference in MSQ and C-PAINAD scores between the experimental and control groups. Accounting for the intracluster correlation, a variance inflation factor of 1.31 will be multiplied to this calculated sample size. Further accounting for a 15% drop-out rate over the period based on two similar studies [13,18], a total number of 61 participants per group is required, resulting in a total proposed sample size of 122. This means we will recruit 15 to 16 participants in each long-term care home.

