### Randomization and allocation concealment

The care home list is generated from the website of the Social and Welfare Department of HK, which includes all local government-funded long-term care homes. An invitation letter has been sent to 75 local long-term care homes that meet the home selection criteria. Based on our previous experience, the response rate will be around 15% to 20%. This means we anticipate that about 11 to 15 care homes will accept our invitation. A random list and a replacement list will be generated. Eight care homes will be randomly selected from all care homes who accept the invitation.

The homes will then be randomized to the control or experimental condition according to the pre-set computer-generated randomization list generalized by a biostatistician who will not be involved in this study. Random group allocations will be sealed in opaque envelopes. Each care home will be viewed as one unit throughout the entire study. As mentioned in the section on home selection criteria, the settings of the home should be similar, and we will not stratify or match the homes during the randomization process. Random allocation will be performed after receiving the homes’ indication of their willingness to join the study. We anticipate that this recruitment process will take about 3 to 4 months. The researcher will then open the random allocation envelopes in order and allocate nursing homes to either the experimental or control condition accordingly. Participants from each long-term care home will be placed into their care homes’ corresponding group to avoid ‘contamination’ effects across participants within the experimental and control conditions. Participant recruitment will be conducted after the care homes have been randomly allocated to either group. Each care home will recruit 15 to 16 participants. We anticipate that it will take about 3 to 4 weeks to complete participant recruitment in each nursing home. The study, including staff training, baseline assessment, and protocol implementation, will start after we have recruited sufficient numbers of participants in each nursing home.

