### Statistical analysis and outcome measurement

Data will be analyzed using the Statistical Package for the Social Sciences (SPSS 19). Descriptive statistics will be generated for the demographic data. Normality assumptions for the variables will be checked. The paired t-test or Wilcoxon’s signed rank test will be used to examine any significant difference in the use of pain treatments and the change in the C-PAINAD score in the experimental group before and after implementation of the protocol. Student’s t-test or the Mann-Whitney U test will be used to examine any significant differences between the control and experimental groups in terms of the outcome variables. For categorical and dichotomous outcome variables, a χ2 test will be used to identify any significant differences between the groups. A *P* value ≤0.05 will be considered statistically significant. Mixed effect modelling (MEM) will be further used to take into account the intracluster correlation, to measure changes in the outcome measures after intervention with respect to its baseline, and to see the effectiveness of the intervention.

Multiple imputations will be adopted to manage all the missing data.

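### The stated 80% power makes no allowance for randomising only eight homes: on 6 between-home degrees of freedom, an unadjusted comparison has about 70% power at effect size 0.65 and about 34% at the stated 0.4

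*Protocol article*

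**What the plan says.** The Sample size section of the protocol article sets the error rates: "With a significance level (α) of 0.05 and power (1-β) 0.8 for a two-sided test". It derives an effect size from the pilot ("After averaging the effect sizes calculated based on these two mean differences, this was equivalent to an effect size of 0.65") and then says that "a more conservative approach of using an effect size of 0.4 was used to calculate the sample size". The result is about 38 residents per group. Clustering enters next: "Accounting for the intracluster correlation, a variance inflation factor of 1.31 will be multiplied to this calculated sample size". The ICC behind that factor is 0.02, although the authors write that "we can only estimate the intracluster coefficient with a range between 0 and 0.1". After a 15% allowance for drop-out the total is 61 per group, or 122 residents at 15 to 16 per home.

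On the number of clusters the section says "We will randomly select eight long-term care homes that agree to join this study". The section on randomisation and allocation concealment adds that "Each care home will be viewed as one unit throughout the entire study", with no stratification or matching. The statistical analysis section lists unadjusted two-group tests and then says "Mixed effect modelling (MEM) will be further used to take into account the intracluster correlation". It names no reference distribution or degrees-of-freedom method for that model.

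**The concern.** A variance inflation factor makes the standard error of the arm difference right when residents in one home resemble each other. It does not change the distribution against which the ratio of difference to standard error is judged. When whole homes are randomised, the error term for the arm effect is the variation between homes, and eight homes in two arms estimate it on 6 degrees of freedom. The two-sided 5% critical value is then 2.447. The calculation behind 38 per group uses about 1.96 (normal) or 1.99 (74 degrees of freedom). The printed 80% therefore belongs to a test with far more information about its error variance than this design supplies.

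If the analysis holds its 5% level, a null result could be read as coming from an 80%-power trial when the power was lower. If the 80% is kept by judging the model against 1.96, the 5% level is no longer secure over the ICC range that the article itself gives.

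**Working it through.** **Inputs from the Sample size section.** Two-sided alpha 0.05; power 0.80; effect size 0.4 stated and 0.65 from the pilot; 38 per group before clustering; ICC 0.02 (range 0 to 0.1); inflation factor 1.31; drop-out 15%; 61 per group; eight homes. Four homes per arm is implied by 61 per group at 15 to 16 per home, but is not stated. The 6 degrees of freedom (8 - 2) do not depend on that split.

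**Step 1: reproduce the plan's figures.** With n = 2(1.960 + 0.842)²/d²:
- d = 0.65 gives 15.70/0.4225 = 37.2, so 38 per group, as printed.
- d = 0.4 gives 15.70/0.16 = 98.1, so 99 per group, not 38.

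The printed 38 therefore reflects 0.65, not the stated 0.4. That is a separate defect, so both effect sizes are carried forward. The rest of the chain is 38 × 1.31 / 0.85 = 58.6, close to the printed 61.

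**Step 2: power formula.** Noncentral t with noncentrality d × √(n_eff/2), where n_eff = residents per arm / design effect and design effect = 1 + (m - 1) × ICC, for m residents per home.

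**Step 3: the plan's own target, n_eff = 38, d = 0.65.** Noncentrality 0.65 × √19 = 2.833.
- 74 degrees of freedom (2 × 38 - 2): 79.9%.
- 6 degrees of freedom: 65.8%.

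**Step 4: what the printed 61 per arm delivers.** 61 × 0.85 = 51.85, about 52 completers per arm, or 13 per home.
- Printed factor 1.31: n_eff = 51.85/1.31 = 39.6; at 0.65 on 6 degrees of freedom, 67.6%.
- Factor recomputed at 13 per home: 1 + 12 × 0.02 = 1.24; n_eff = 52/1.24 = 41.9; noncentrality at 0.65 = 2.976.

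| Effect size (n_eff 41.9) | 102 df (2 × 52 - 2) | 6 df |
|---|---|---|
| 0.65 | 83.8% | 70.0% |
| 0.4 | 44.2% | 33.9% |

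A simulation with four homes of 13 per arm gives 70.1% at 0.65 with a t-test on the eight home means. A random-intercept analysis, using pooled residual degrees of freedom whenever the home variance is estimated as zero, also gives about 70%.

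**Step 5: over the plan's ICC range** (13 per home, 6 df):

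| ICC | Design effect | n_eff | Power at 0.65 | Power at 0.4 |
|---|---|---|---|---|
| 0 | 1.00 | 52.0 | 79% | 40% |
| 0.02 | 1.24 | 41.9 | 70% | 34% |
| 0.05 | 1.60 | 32.5 | 59% | 28% |
| 0.1 | 2.20 | 23.6 | 47% | 21% |

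**Step 6: effect detectable with 80% power.** On 6 degrees of freedom the noncentrality must be about 3.37, so d = 3.37/√(n_eff/2): 0.74 at n_eff 41.9 and 0.77 at n_eff 38 (both ICC 0.02). At the ends of the range it is 3.37/√26 = 0.66 (ICC 0) and 3.37/√11.8 = 0.98 (ICC 0.1).

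**Step 7: the same random-intercept analysis judged against 1.96** (simulation). At ICC 0.02 and 0.65, power is about 81%. Type I error is about 5.6% at ICC 0.02, 7.1% at 0.05 and 8.7% at 0.1 (runs between 8.5% and 8.7%).

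**The case against.** A reader might infer from these figures that the trial simply has 66% to 70% power. The documents do not support that, for three reasons.

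First, the article fixes no reference distribution for the mixed model. At the assumed ICC of 0.02, a 1.96 reference gives about 81% power with type I error of about 5.6%, close to nominal. The stricter random-intercept rule of Step 4 rejects only about 4% of the time under the null, so part of its loss at that ICC is conservatism. This stands for ICC 0.02 exactly. It does not rescue the claim over the range that the authors say they cannot narrow.

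Second, the calculation uses one unadjusted outcome per resident, whereas the plan has four weekly baseline and twelve weekly follow-up measurements and a model for change from baseline. No correlation is given. If baseline adjustment removed a share r² of the variance (an assumption), power at 0.65 on 6 degrees of freedom would be about 74% at r = 0.3, 82% at r = 0.5 and 93% at r = 0.7. This stands too: 70% is not the power of the full planned analysis. But the printed 80% takes no such credit either, so like is compared with like.

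Third, 66% uses n_eff = 38. The printed 61 per arm delivers slightly more, which gives 68% to 70%.

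It would also go too far to fault the article for naming no degrees-of-freedom method, since that choice commonly sits in a statistical analysis plan. Nor do the unadjusted t-tests in the analysis section justify the 80%: they ignore clustering, while the sizing itself inflates for it.

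**Conclusion.** The point holds in conditional form. The 80% comes from a resident-level calculation with a variance correction, and nothing in it allows for eight homes. For an unadjusted comparison that keeps the 5% level over the plan's ICC range, and at ICC 0.02 after 15% drop-out, power at 0.65 is about 70% (68% with the printed factor), against about 84% by the plan's own method. At the stated 0.4 the corresponding figures are about 34% and 44%. At 0.65 on 6 degrees of freedom, power stays below 80% throughout the ICC range.

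This assumes four homes per arm, equal home sizes, approximately normal home means and one summary outcome per resident.

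The larger defect in the same paragraph is that 38 per group does not follow from an effect size of 0.4. The two are distinct: settling the effect size at 0.65 would still leave the shortfall described here.

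**What to change.** In the Sample size section, keep eight homes and 122 residents and replace the 80% with power computed from a t reference on 6 degrees of freedom, at ICC 0, 0.02 and 0.1. At 0.65 these are about 79%, 70% and 47%; at 0.4, about 40%, 34% and 21%. Alternatively, state the effect detectable with 80% power, about 0.74 to 0.77 at ICC 0.02. Label the figures as taking no credit for baseline adjustment or repeated measures, which could raise them. Make the change together with the correction of the 0.4-versus-38 mismatch, because both rewrite the same calculation.

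To match, add one sentence, here or in the statistical analysis plan, that the arm effect in the mixed model is judged with small-sample, between-home degrees of freedom (Satterthwaite, Kenward-Roger or a t-test on the eight home means).

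The cost is a less favourable stated power and wider confidence intervals. No homes, residents or procedures are added.

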### Randomization and allocation concealment

The care home list is generated from the website of the Social and Welfare Department of HK, which includes all local government-funded long-term care homes. An invitation letter has been sent to 75 local long-term care homes that meet the home selection criteria. Based on our previous experience, the response rate will be around 15% to 20%. This means we anticipate that about 11 to 15 care homes will accept our invitation. A random list and a replacement list will be generated. Eight care homes will be randomly selected from all care homes who accept the invitation.

The homes will then be randomized to the control or experimental condition according to the pre-set computer-generated randomization list generalized by a biostatistician who will not be involved in this study. Random group allocations will be sealed in opaque envelopes. Each care home will be viewed as one unit throughout the entire study. As mentioned in the section on home selection criteria, the settings of the home should be similar, and we will not stratify or match the homes during the randomization process. Random allocation will be performed after receiving the homes’ indication of their willingness to join the study. We anticipate that this recruitment process will take about 3 to 4 months. The researcher will then open the random allocation envelopes in order and allocate nursing homes to either the experimental or control condition accordingly. Participants from each long-term care home will be placed into their care homes’ corresponding group to avoid ‘contamination’ effects across participants within the experimental and control conditions. Participant recruitment will be conducted after the care homes have been randomly allocated to either group. Each care home will recruit 15 to 16 participants. We anticipate that it will take about 3 to 4 weeks to complete participant recruitment in each nursing home. The study, including staff training, baseline assessment, and protocol implementation, will start after we have recruited sufficient numbers of participants in each nursing home.

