#### *Inclusion criteria for long-term care homes*

The long-term care homes, funded by the government, must be under the Social and Welfare Department of Hong Kong (HK) and thus meet a set of standard criteria as set by the HK Government. The staffing pattern, staff-resident ratio, bed space, the other service criteria of the facilities, and the nature of the residents are therefore similar in that they have to meet government standards. Additionally, the total number of residents must be 100 or above so as to maximize the chance of recruiting a sufficient number of participants in each care home (that is 15 to 16 - please refer to sample size for details).

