### Intervention

Residents who meet the sample selection criteria will be recruited. We will interview potential participants and their relatives to explain the purpose of the project. Their cognitive level will be assessed with the C-MMSE, whereas their communication ability will be assessed by two items in the Hong Kong version of the interRAI-HC assessment during participant recruitment. Additionally, their verbal fluency will be assessed by the Modified Fuld Verbal Fluency Test (M-FVFT) [23]. Demographic data, pain-related diagnoses, and medical history will be collected by reviewing participants’ medical records.

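### Residents are recruited after the researcher has opened their home's allocation, with no stated blinding of recruiters, so randomisation does not protect which eligible residents enter each arm

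*Protocol article*

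**What the plan says.** The order of events is set out in the Protocol article under Randomization and allocation concealment.

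- Homes are the randomised unit: "Each care home will be viewed as one unit throughout the entire study".
- They are randomised once they agree to take part: "Random allocation will be performed after receiving the homes’ indication of their willingness to join the study".
- The envelopes are opened: "The researcher will then open the random allocation envelopes in order and allocate nursing homes to either the experimental or control condition accordingly".
- Residents come next: "Participant recruitment will be conducted after the care homes have been randomly allocated to either group". The target is fixed ("Each care home will recruit 15 to 16 participants") and so is the expected duration: "We anticipate that it will take about 3 to 4 weeks to complete participant recruitment in each nursing home".

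Under Intervention, the research team makes the approach: "We will interview potential participants and their relatives to explain the purpose of the project". Ethical considerations requires proxy consent from guardians or next of kin and does not place it before allocation. The Blinding section covers two research assistants, who are responsible for the assessment measures. It does not mention the people who identify, approach or consent residents.

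**The concern.** The opaque envelopes conceal the arm up to the moment a home is allocated. They do nothing for residents, who enter afterwards. Three steps can then depend on the arm:

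- **Who is approached.** Each home supplies 15 to 16 residents. The article describes no closed list of eligible residents and no random or consecutive draw from one.
- **Who is judged eligible.** Stable general health, an open-ended list of pain-related diagnoses and a forecast of frequent hospital admission all call for judgement.
- **Which relatives agree.** A relative may respond differently to an active pain programme than to usual care.

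The outcomes are analgesic use, non-pharmacological treatment and pain behaviour. If experimental homes enrolled residents who were more likely to be treated or to respond, the estimated effect would move with no true effect present. With only eight homes, neither stratified nor matched, such a shift would be hard to tell from chance imbalance.

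**Working it through.** **Sequence.** Setting the sections side by side gives this order: home agrees; envelope opened by the researcher; residents recruited over 3 to 4 weeks; training and baseline weeks; implementation. No section places identification or consent before the envelope. The order is a stated design choice, not a detail left to a fuller document.

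**Size.** The plan has no figure for selection bias to reproduce, so what follows is an illustration. The shift b is an assumption, shown over a range. It means the between-arm difference, in SD units, that is left in the tested outcome after any baseline adjustment.

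Inputs from the Sample size section: 122 residents, eight homes (four per arm), 15% drop-out, intracluster correlation 0.02 within a range of 0 to 0.1, two-sided 5% test.

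- Analysed per home: m = 122/8 × 0.85 = 15.25 × 0.85 = 12.96, about 13.
- Design effect: 1 + (m − 1) × ICC. At 0.02 this is 1 + 11.96 × 0.02 = 1.24. At 0.1 it is 1 + 11.96 × 0.1 = 2.20.
- Standard error of the arm difference: sqrt(2 × design effect/(4 × m)). At 0.02 this is sqrt(2 × 1.24/51.84) = 0.219 SD. At 0.1 it is sqrt(2 × 2.20/51.84) = 0.291 SD.
- Reference distribution: t with 8 − 2 = 6 degrees of freedom, because homes are the independent units. The critical value is 2.447.
- False-positive rate: the probability that a noncentral t on 6 df, with noncentrality b/SE, lies outside ±2.447.

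| Residual shift b (SD, assumed) | ICC 0.02: b/SE | ICC 0.02: rate | ICC 0.1: b/SE | ICC 0.1: rate |
|---|---|---|---|---|
| 0 | 0 | 5% | 0 | 5% |
| 0.1 | 0.46 | 6.8% | 0.34 | 6.0% |
| 0.2 | 0.91 | 12% | 0.69 | 9.0% |
| 0.3 | 1.37 | 21% | 1.03 | 14% |

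A normal reference would give about 15% in place of 12% at b = 0.2 and ICC 0.02. With eight homes the t reference is the more suitable one.

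**Effect on sample size.** Recruiting before the envelopes are opened changes no input to the sample size calculation.

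**The case against.** Four points can fairly be made for the plan.

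- **Much of eligibility is fixed.** Age, length of stay, a formal dementia diagnosis, a communication score of at least 5, and no fracture or emergency admission in the past 3 months leave little room. The requirement on home size ("the total number of residents must be 100 or above so as to maximize the chance of recruiting a sufficient number of participants") suggests that eligible residents may be scarce. If the eligible number per home, which is not given, is close to 15 or 16, there is little picking to do. This stands as a limit on selection by recruiters. It does not touch differential consent.
- **Knowledge of the arm is documented only for the researcher.** The article does not say when homes, staff or relatives are told. Both arms receive four workshops, and these start after recruitment, so the arms may look alike to families at consent. This stands: knowledge beyond the researcher is inference.
- **All three outcomes are measured in four baseline weeks, and a mixed model assesses change from baseline.** A shift in baseline pain or analgesic use would be seen and largely adjusted for. This stands for measured factors. It does not reach expected response or readiness to accept treatment. The between-group t, Mann-Whitney and chi-squared tests are listed with no stated baseline adjustment. The baseline weeks also follow allocation and overlap staff training.
- **Outcome assessment is blinded.** This is true, and it guards against biased measurement. It cannot correct who was enrolled.

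A reader might infer that randomisation gives the trial no protection at all. The documents do not support that. The allocation list comes from a biostatistician not involved in the study and sits in opaque envelopes, so the comparison of homes stays protected. Nor do they show that differential selection will happen, only that the order of steps permits it.

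**Conclusion.** The concern holds at resident level. The plan opens each home's allocation before its residents are recruited and states no blinding for the people who recruit them, so arm-dependent selection and consent are possible and can be only partly corrected in analysis.

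The documents give no size for the harm. On the assumption that 0.1 to 0.3 SD remains after adjustment, the two-sided false-positive rate is about 7% to 21% at an intracluster correlation of 0.02, and about 6% to 14% at 0.1, against a nominal 5%. These rates rest on 13 analysed residents per home and a t reference on 6 degrees of freedom. A smaller residual shift would do correspondingly less damage.

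The point deserves action because the bias is avoidable and the remedy cheap. According to Trial status, care homes are still being recruited.

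**What to change.** In Randomization and allocation concealment, reverse the two steps. In each home, complete screening, proxy consent and a closed list of 15 to 16 residents before that home's envelope is opened. Have the envelopes held by someone outside the recruiting team until the list is signed off.

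The cost is a wording change and a re-ordering of existing work. The 3 to 4 weeks of resident recruitment stay the same, and the plan already starts nothing until enough residents have been recruited. The downside is that homes learn their arm about 3 to 4 weeks later and a few may withdraw. Only 11 to 15 homes are expected to accept, so such losses matter, but the section already provides for a replacement list.

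If this is not feasible, have existing personnel who are blinded to allocation carry out recruitment, drawing residents at random or consecutively from the full eligible list. Report the numbers eligible, approached and consented by home and arm. This limits selection by recruiters. It does not fully remove differential consent if relatives know the arm.
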